## Abstract

The objective of this study is to present the protocol of a
*cluster* randomized clinical trial to be conducted through
the TeleICU project - Qualification of Intensive Care by Telemedicine. The study
will consist of a cluster randomized clinical trial, open label, in pediatric
intensive care units, with an allocation ratio of 1:1, to compare the
intervention group (support of Telemedicine for patients admitted to the
pediatric intensive care unit) with a control group (pediatric intensive care
unit usual care). The study proposed to select 16 pediatric intensive care
units, including 100 participants per site, with a total of 1,600 participants.
The intervention group will receive telerounds from Monday to Friday and will
have specialists and continuing education activities available. The primary
outcome measure will be the length of stay in the pediatric intensive care unit,
defined as the difference between the date of discharge of the participant and
the date of admission to the intensive care unit. The secondary outcomes will be
mortality rate, invasive mechanical ventilation-free days, days using
antibiotics, days using vasoactive drugs and days using sedoanalgesia. This
study will be conducted in accordance with Resolution 466/12 of the National
Health Council, with approval by the Research Ethics Committee of the
institutions involved. The present study has the potential to reproduce studies
on Telemedicine in intensive care and may make important contributions to care
in intensive care units in Brazil and other settings. If Telemedicine shows
positive clinical care results compared to conventional treatment, more
pediatric patients may benefit.

**ClinicalTrials.gov registry:** NCT05260710

## INTRODUCTION

### Context and rationale

Intensive care units (ICUs) are critical hospital areas marked by great
complexity in health care^(1)^
due to the provision of care to patients with more severe clinical
conditions.^(2)^ The
attention to these patients demands the appropriation of several specific
domains of knowledge.^(3)^ From
this perspective, the specialization and qualification of human resources is
essential for improving the performance of ICUs, both in terms of quality of
care and management.^(4)^ Studies
have shown better care results in ICUs that have intensivist professionals with
specific education and training.^(5,6)^

Despite the positive impact of specialized care, there is a shortage of
specialists in Brazilian ICUs.^(7,8)^ According to
the *Instituto Brasileiro de Geografia e Estatística*
(IBGE), there is inequity in the distribution of intensivist professionals in
Brazil,^(9)^ since it is
a country with a large demographic area and unequal distribution of resources
among regions,^(10)^ especially
with regard to the public and private health systems.^(11)^ The shortage of these professionals is still
a reality in many Brazilian centers, even with the existence of specific
requirements for care in ICUs.^(12)^

Given this scenario, Telemedicine has been identified as a promising tool in the
qualification of health care.^(13,14)^ In the
context of ICUs, Telemedicine has also been identified as a tool that reduces
the length of stay,^(15,16)^ decreases mortality in the
units,^(15-17)^ reduces costs,^(15)^ increases satisfaction with
care,^(18)^ and is
complementary to bedside professionals.^(19)^ Furthermore, its use has the potential to compensate
for the lack of intensivists in ICUs because it supports generalist
teams.^(20)^

Although there are studies that indicate the effectiveness of Telemedicine in
ICUs in many countries,^(21^.^22)^
its impact is not yet consolidated in the literature,^(18,23,24)^ especially in regard to
pediatric ICUs. In Brazil, there is a need for more robust studies with
well-designed methodologies that demonstrate the results of the use of
Telemedicine in ICUs compared to conventional care to build solid evidence of
the use of this technology.

Within the Brazilian Unified Health System (SUS - *Sistema Único de
Saúde*), there are several opportunities for the development
and implementation of Telemedicine. Thus, through the Support Program for
Institutional Development of the Unified Health System (PROADI-SUS -
*Programa de Apoio ao Desenvolvimento Institucional do Sistema
Único de Saúde*), the “TeleICU project - Qualification
of Intensive Care by Telemedicine” was developed. In general, the project uses
Telemedicine in the form of multiprofessional telerounds for distance education
(DE) and discussion of clinical cases in remote ICUs, aiming to systematize
care, qualify care, reduce risks for hospitalized patients and improve care
indicators of the partner ICUs.^(25)^

### Objectives

To present the protocol of a *cluster* randomized clinical trial
(RCT) that will be conducted through the TeleICU project. This RCT aims to
evaluate the length of hospital stay in pediatric ICUs, with the secondary
objectives of assessing the mortality rate, invasive mechanical ventilation
(IMV)-free days and duration of use of vasoactive drugs, broad-spectrum
antibiotics and sedation/analgesia.

## METHODS

### Study design

The present protocol refers to a study designed as an RCT, by cluster, open
label, in pediatric ICUs, with an allocation ratio of 1:1, in which the
hospitals are the clusters, to perform the comparison of the group intervention
(support of Telemedicine for patients admitted to the pediatric ICU) with a
control group (usual care in the pediatric ICU).

The RCT was registered in the Brazilian Registry of Clinical Trials (ReBEC) on
March 22, 2022, and the present protocol provides additional details on the
study design and methodology, based on the CONSORT 2010 Statement.^(26-28)^

### Intervention (Telemedicine)

The intervention group, during the data collection period, will receive
telerounds from Monday to Friday and will have specialists available on demand
(as cases and specific needs arise, the pediatric ICUs may request evaluation by
specialists from the proposing institution) and continuing education activities.
The telerounds will be case discussions with pediatric intensivists at a
distance and doctors of other specialties on demand for the debate on conduct
based on the best scientific evidence. The intensivists of the project will
connect through a telemedicine CART (Figure 1S - Supplementary Material) with
the pediatric ICU team of the participating centers daily, from Monday to
Friday, to perform medical consultations at the bedside to establish diagnoses,
guide the therapeutic conduct and perform clinical follow-up.

The intensivist of the project will record the appointments on a digital
platform, especially designed for the activity. A treatment plan will be
suggested by the project team (clinical management recommendations). The
physician of the participating center will be free to decide whether to accept
the recommendations. These recommendations will be reassessed 24 hours later in
the next teleround. The proposal is to maintain horizontal care, in which the
patient is monitored from the first day of hospitalization until discharge.

Concurrently with the period of application of the intervention, continuing
education activities will be made available to all professionals of the
participating centers’ teams. Education activities will be held monthly and will
consist of video classes, discussions of complex cases and DE courses. The video
classes will be made available synchronously and asynchronously, with topics
chosen according to the needs of each center. The discussions of complex cases
will be meetings in which each participating center will be responsible for
choosing a case considered a challenge to the team, and medical specialists will
be invited to participate in the discussions. The DE courses will be developed
by the proposing institution and will be available on a platform specific to the
study, with specific themes to qualify care in pediatric intensive care. These
courses may be attended at any time by staff of the participating centers.

### Control

The control group will initially maintain the usual face-to-face management
offered in the pediatric ICUs at the participating centers and will perform data
collection. After completing the collection stage, the intervention will be
offered along the same lines as the intervention group. The aim is to provide
opportunities for the provision of Telemedicine and to draw on the expertise of
the professionals of the proposing institution to enhance the care in all the
participating centers.

### Selection of pediatric intensive care units and randomization

For the selection of hospitals, the following methodology was used: generate a
list of all Brazilian public hospitals with 100% dedication to SUS care and a
pediatric ICU; classify the pediatric ICUs according to their complexity, the
project selected the type II pediatric ICUs;^(29)^ categorize the pediatric ICUs according to
the number of beds, the pediatric ICUs with 4 to 20 beds moved to the next
stage; contact all eligible pediatric ICUs (considering steps 1, 2 and 3) by
telephone or e-mail, inviting the person in charge to engage in the project;
send a questionnaire to assess feasibility to all those responsible for the
pediatric ICUs who expressed interest in participating in the project;
considering the answers to the feasibility questionnaire and schedule a meeting
with the eligible pediatric ICUs together with the team (pediatric intensivist,
nurse, researcher and information technology professional) of Hospital Moinhos
de Vento (HMV), so that each specialist can be scored according to
preestablished criteria; prepare a ranking with the evaluations of the hospitals
and select the 16 centers with the highest scores to participate in the
project.^(30)^ It is
noteworthy that pediatric ICUs (PICUs) that do not have approval from the
Research Ethics Committees involved will be excluded.

Subsequently, the selected PICUs will be randomly allocated to the intervention
group or control group at a 1:1 ratio, with blocks of varying sizes (two to
four), with dichotomous stratification by the estimated median length of stay in
2020 and 2021 (> 11 *versus* ⋦ 11 days).^(31)^ The generation of the
randomization sequence for each stratum will be the responsibility of the
statistician of the proposing institution, using R software, ensuring the
blinding of the allocation sequence of researchers from the proposing
institution.

### Sample size

A total of 16 pediatric ICUs, including 100 participants per location, for a
total of 1,600 participants will be selected to detect a decrease of 2.3 days of
hospitalization in the intervention units compared to the control unit. To
consider the standard deviation (SD), the data from the TeleICU project
indicators were used for a SD of 6.2 days in the control units and 7.1 in the
intervention group, in addition to an intraclass correlation coefficient of
0.05, power of 80% and alpha of 5%. WinPepi software, version 11.65, was chosen
to determine the sample size calculation.

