### Statistical analysis

Statistical analyses will be performed both by intention-to-treat and by
protocol, considering that the study design is a cluster RCT, and data from the
observed pediatric ICUs will be analyzed.

The description of the information regarding the PICUs and the characteristics of
the participants will be presented for the control and intervention groups, in
which the categorical variables will be presented by absolute and relative
frequency, while the continuous variables will be first evaluated for normality
by means of visual verification of histogram and Shapiro‒Wilk test and presented
as the mean and SD or median and interquartile range (IQR), depending on the
data distribution, as shown in table 1S (Supplementary Material).

For the primary outcome of the study, a noninferiority analysis will be performed
through modeling, considering that the data are correlated in each ICU, by
generalized mixed models adjusted for variables of interest to the researchers.
Regarding the secondary outcomes, correlated data models will also be used;
however, the probability distribution of each outcome will be taken into
account. Table 2S (Supplementary Material) describes the data to be
analyzed.

Sensitivity analyses will be conducted only for the primary outcome in the
intervention group to verify whether adherence to teleround can impact the
length of stay.

We will also analyze some exploratory results regarding the days of IMV use,
number of days off for each ventilatory support and days off the use of
medications such as antibiotics, sedoanalgesia, antifungal and antiviral, water
balance during hospitalization and verification of permanence in hospital
intensive care (use of IMV or sedoanalgesia) in participants who spent at least
8 days in the pediatric ICU, as shown in table 3S (Supplementary Material).

All statistical analyses will be performed considering a significance level of
0.05. The software to perform all the analyses will be the R program, version
4.2.1 or a later version.

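### The stated 80% power makes no allowance for having only 8 clusters per arm; on the same inputs a test with between-cluster degrees of freedom has about 75%

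*Protocol article*

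**What the plan says.** The Sample size section plans 16 units with 100 patients each. It gives the aim in these words: "total of 1,600 participants will be selected to detect a decrease of 2.3 days of"; the outcome is stay in the unit. The standard deviations come from the project's own data: "indicators were used for a SD of 6.2 days in the control units and 7.1 in the". The second figure belongs to the intervention arm. The intraclass correlation and the error rates then appear as "0.05, power of 80% and alpha of 5%. WinPepi software, version 11.65, was chosen", where the leading figure is the intraclass correlation. Sidedness is not stated. The section mentions no degrees of freedom and no allowance for a small number of clusters.

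Study design makes the hospital the cluster, with 1:1 allocation. The section on selection of units and randomization adds "dichotomous stratification by the estimated median length of stay in"; the data are from two earlier calendar years and the cut is at 11 days. Statistical analysis plans "generalized mixed models adjusted for variables of interest to the researchers" for the primary outcome, taking account of correlation within each unit, and sets a 0.05 significance level for all analyses. It names no reference distribution and no method for degrees of freedom.

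**The concern.** In a trial that randomises 16 hospitals, the error of the treatment comparison is estimated from the variation between 16 unit means, however many patients each unit contributes. The two-sided 5% critical value is therefore about 2.145 (14 degrees of freedom) or 2.160 (13), not 1.96. A calculation that inflates an individually randomised sample size by a design effect and keeps normal quantiles misses this. The loss is small with many clusters but not with 8 per arm.

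What is at stake is whether the stated 80% power and 5% alpha can hold together. If they cannot, the chance of missing a true 2.3-day reduction is nearer 25% than the 20% that readers are told.

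**Working it through.** **Inputs** (Sample size and Study design): difference 2.3 days; SDs 6.2 and 7.1 days; intraclass correlation 0.05; 100 patients per unit; 8 units per arm; alpha 5%; power 80%.

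**Reproducing the stated size, with normal quantiles and two-sided 5%**
- Sum of variances: 6.2² + 7.1² = 38.44 + 50.41 = 88.85.
- Per arm without clustering: (1.96 + 0.8416)² × 88.85 / 2.3² = 131.8.
- Design effect: 1 + 99 × 0.05 = 5.95.
- Per arm with clustering: 131.8 × 5.95 = 784, that is 7.84 clusters of 100, rounded up to 8. This gives the stated 16 units and 1,600 patients.
- Standard error at 8 × 100 per arm: √(88.85 × 5.95 / 800) = 0.8129 days.
- Ratio of difference to standard error: 2.3 / 0.8129 = 2.829.
- Normal-quantile power: Φ(2.829 − 1.960) = 80.8%.

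A one-sided 5% test gives 88.2% by the same formula, so two-sided is the reading that fits the stated 80%.

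**Same inputs, between-cluster degrees of freedom**

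Degrees of freedom are 2 × (8 − 1) = 14, or 13 with the stratum fitted. Power comes from the noncentral t distribution with noncentrality 2.829.

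| Reference | Critical value | Power for 2.3 days | Difference with 80% power |
|---|---|---|---|
| Normal | 1.960 | 80.8% | (2.3 days stated) |
| t, 14 df | 2.145 | 74.9% | 3.013 × 0.8129 = 2.45 days |
| t, 13 df | 2.160 | 74.4% | 3.031 × 0.8129 = 2.46 days |

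Allowing for the unequal SDs with Welch degrees of freedom (13.75) gives 74.8%.

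**What would reach 80% on the t reference**
- Nine units per arm (18 units, 1,800 patients): 80.4%, or 80.1% with the stratum fitted.
- Eight units per arm: 300 patients per unit give 79.5% and 500 give 80.4%. The number of units is the limit, not the number of patients.
- Eight units of 100 with a smaller between-cluster variance: the standard error becomes √(88.85 × (0.05 × (1 − r) + 0.0095) / 8), where r is the fraction of between-cluster variance removed and 0.0095 is 0.95/100. At r = 0.15 it is 0.7600, the ratio is 3.027, and power at 13 df is 79.9%. The fraction r is an assumption; the article gives no figure for it.

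**Conditional check on the 5% level**

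If the treatment effect were referred to 1.96, the probability of rejection under the null would be 2 × P(t₁₄ > 1.96) = 7.0% with a REML-type variance. With a maximum-likelihood variance it would be 2 × P(t₁₄ > 1.96 × √(14/16)) = 8.8%. Simulation of balanced data with 300,000 replicates gave the same two figures.

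**The case against.** Four points can fairly be made for the plan.

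- **The stated size reproduces.** This is true. The calculation is a standard design-effect calculation carried out correctly. The weakness is a missing allowance for few clusters, not a slip in arithmetic. That the software used normal quantiles is inferred from the match, not stated.
- **Stratification and covariates may recover the power.** The stratification factor is past unit-level length of stay, which is close to the primary outcome, and the primary model is adjusted. Charging the stratum one degree of freedom while crediting it with no precision is one-sided. Removing about 15% of between-cluster variance would restore 80% at 13 df. This stands as a limit on how definite the 75% is. It does not rescue the stated figure, because the sample size statement claims no such gain. Unequal unit sizes, likely with 4 to 20 beds, would push power the other way.
- **The effect is small.** The detectable difference moves by about 0.15 days, and the article does not present 2.3 days as a clinical threshold. This is fair, and it is why the remedy is a restatement and not a redesign.
- **The degrees-of-freedom method belongs in the analysis plan.** This also stands. A reader might infer from the words on generalized mixed models that the trial will run at 7% to 9% type I error. The article does not support that: it names neither a normal reference nor maximum-likelihood variance, and an analysis plan that is not shown may settle the matter. The power statement does not depend on this, since choosing the correct degrees of freedom is what makes 80% too high.

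**Conclusion.** The concern holds for the power statement. On the article's own inputs, 16 units of 100 do not give 80% power and a 5% level together. A test that keeps the level has about 75% power for 2.3 days, and 80% power for about 2.45 days.

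This rests on a two-sided test, equal units of 100, approximately normal unit means, an intraclass correlation of 0.05, and no gain from stratification or covariates. A documented gain would raise the figure; unequal unit sizes would lower it. Inflated type I error remains a risk only if a normal reference is used, and is not an error that the article states. The design can stand; its stated power is about 5 to 6 percentage points too high.

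**What to change.** In the Sample size section, state that the test is two-sided and do one of the following for 16 units of 100:

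1. Give power as about 75% for 2.3 days, or give about 2.45 days as the difference detectable with 80% power.
2. Keep 80% for 2.3 days, but state and justify the reduction in between-cluster variance expected from the stratum and covariates (about 15% is needed), labelled as an assumption.

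In either case, fix before analysis that the primary test uses between-cluster degrees of freedom, in the article or the analysis plan. Suitable choices are Kenward-Roger or Satterthwaite for a linear mixed model, and a t reference with 13 df or a permutation test of allocation within strata for a generalized one. If the analysis plan already does this, only the power statement needs changing.

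The cost is a slightly less favourable stated power or detectable difference, and slightly wider intervals than a normal reference would give. No additional units or patients are required.

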### Eligibility of participants

The eligibility criteria for the participants are patients admitted to the
selected pediatric ICUs ≥ 29 days and < 18 years of age, with a stay
of more than 24 hours and, in case of death, with a stay of more than 8
hours.

The exclusion criteria are patients with incomplete medical records or missing
data, with a stay > 90 days in the ICU, who are in the intervention cluster
and did not receive telemedicine care, and those whose guardians did not agree
to participate in the study and/or did not sign the informed consent.

The recruitment of study units and study participants will follow the criteria of
the 2010 statement of the Consolidated Standards of Reporting Trials (CONSORT)
for cluster randomized trials and is detailed in figure 1.

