#### Pilot data collection

After the training, all centers will conduct pilot data collection for 2
weeks. This time was based on the previous experience of the TeleICU project
with other pediatric ICUs. The objective is to accompany the collector until
he or she reaches minimum quality conditions and to provide time for
efficiency in data collection to be achieved. This is a form of training and
adaptation for the application of data collection forms. During this time,
the weaknesses of each collector will be identified, and adjustments will be
made according to the specific need of each collector. The centers
participating in the control group will start the official collection after
2 weeks, while the centers participating in the intervention group will have
another 2 weeks of pilot training with the addition of telerounds in their
routine. After this period, the centers will begin the official data
collection. All data from the pilot phase will be excluded from the database
and will be stored based on the rules of the General Data Protection Law
(LGPD - *Lei Geral de Proteção de
Dados*).^(34)^

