#### Treatment of missing data

We assume that there will be missing data in the research variables. However,
monitoring will be performed regularly to check for missing data and
inconsistencies, and based on the evidence, the monitors will contact the
collectors to make the necessary adjustments.

Data analyses will be performed with the information that is available after
the monitoring. Thus, the primary and secondary outcomes will not have data
imputation.

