### Outcomes

The primary outcome measure will be the length of stay of the patients in the
PICU, defined as the difference between the date of discharge and the date of
admission to the ICU. The secondary outcomes will be mortality rate, IMV-free
days, days using antibiotics, days using vasoactive drugs and days using
sedoanalgesia.

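### The open-ended missing-data exclusion conflicts with the available-data rule and the intention-to-treat analysis, and read literally drops children whose length of stay is known

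*Protocol article*

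**What the plan says.** Four statements in the protocol article bear on this point.

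- **Eligibility of participants:** "The exclusion criteria are patients with incomplete medical records or missing" data. No variable, amount of missingness or time of assessment is given. The same sentence has a separate rule for long stays ("with a stay > 90 days in the ICU").
- **Treatment of missing data:** "We assume that there will be missing data in the research variables". After monitors have chased the gaps, "Data analyses will be performed with the information that is available after" that monitoring, and "the primary and secondary outcomes will not have data" imputation.
- **Statistical analysis:** "Statistical analyses will be performed both by intention-to-treat and by" protocol.
- **Outcomes:** the primary outcome is length of stay in the PICU, "defined as the difference between the date of discharge and the date of" admission.

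The trial is open label and randomises hospitals (Study design).

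**The concern.** One section removes a child because data are missing. Another expects children with missing data to be in the analysis. An analyst cannot follow both, and the choice decides who is analysed for the primary outcome.

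Whether a record is complete is learned only after admission, and for much of it at or after discharge. The exclusion is therefore applied after the clusters were randomised and while care is being given under a known allocation. The monitors who check the forms also follow teleround adherence in the intervention arm (Data collection monitoring team), so they know the arm. If completeness is related to stay, severity or arm, the children left in the two arms are no longer those that randomisation made comparable. The intention-to-treat label would then promise more than the analysis delivers.

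**Working it through.** **1. The rules side by side.** Take a child with both PICU dates recorded but antibiotic days blank.

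| Rule | Primary outcome | Antibiotic days |
|---|---|---|
| Eligibility exclusion, read literally | excluded | excluded |
| Available-data rule | included | not analysed, not imputed |
| Intention-to-treat | included | as far as recorded |

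If the first row governs, no missing data are left for the second to handle. If the second governs, the exclusion has no effect. The blank has no bearing on the primary outcome, which is a difference of two known dates.

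**2. The plan's sample size.** Inputs from Sample size: difference 2.3 days, SDs 6.2 and 7.1, intraclass correlation 0.05, 100 children per unit, 80% power, alpha 5% (taken as two-sided).

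- Per arm without clustering: (6.2² + 7.1²)(1.960 + 0.842)² / 2.3² = 131.8.
- Design effect: 1 + 99 × 0.05 = 5.95.
- Per arm with clustering: 131.8 × 5.95 = 784.4, or 7.84 units, rounded up to 8. Total 2 × 8 × 100 = 1,600, as stated.

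**3. Power if children are excluded.** Assume 8 units per arm, exclusion unrelated to stay, and no replacement. With m children left per unit, DE = 1 + (m − 1) × 0.05, SE = √[(6.2² + 7.1²) × DE / (8m)], and power = Φ(2.3/SE − 1.960).

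| Excluded | m | DE | Effective n per arm (8m/DE) | Power |
|---|---|---|---|---|
| 0% | 100 | 5.95 | 134.5 | 80.8% |
| 10% | 90 | 5.45 | 132.1 | 80.1% |
| 20% | 80 | 4.95 | 129.3 | 79.2% |
| 30% | 70 | 4.45 | 125.8 | 78.1% |

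A t reference with 14 degrees of freedom lowers the level (74.9% at 0%, 72.1% at 30%), but the loss from exclusion is equally small.

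**4. Can the direction of selection be found?** The documents give no missingness rate by stay or arm, so only assumed mechanisms can be tried. Assume lognormal stays with the plan's SDs, a true difference of 2.3 days and a control mean of 8 or 11 days (simulated difference without exclusion: 2.29 and 2.30).

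- *Longer stays more often incomplete.* Each day carries the same chance, 0.5% to 2%, of a gap that excludes the child. This loses 4–19% of control and 3–15% of intervention children. The control mean falls by about 0.2–0.7 days and the difference becomes about 2.33–2.45.
- *Shorter stays more often incomplete.* The exclusion probability is 0.3·exp(−stay/5). This loses 5–9% and 9–14%. Mean stay rises by about 0.2–0.5 days and the difference becomes about 2.14–2.15.
- *Gap rates that differ by arm, with no true effect.* Assume gamma stays and a daily gap rate λ of 1% in control and 0.5% in intervention. The retained mean is mean/(1 + λθ), with θ = SD²/mean. Mean 8, SD 6.2: θ = 4.805, giving 7.63 against 7.81, a spurious 0.18 days. Mean 11, SD 7.1: θ = 4.583, giving 10.52 against 10.75, a spurious 0.24 days. Here control looks shorter, which works against telemedicine. Swapping the rates reverses the sign, and equal rates give zero.

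The sign follows the assumption each time.

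**The case against.** **A narrower reading.** The clause may mean only records too poor to use, with the available-data rule covering ordinary gaps. That would largely remove the conflict, and a fuller protocol or analysis plan may say so. But the article states both rules and does not write the limit. The defect is thus an undefined threshold that reads literally as a complete-record rule. It is not proof that every blank will lead to exclusion.

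**Data-quality safeguards.** Both arms are trained in REDCap, pilot their collection, and have weekly review with queries and follow-up contact. This should keep gaps few and similar between arms. It lowers the likely size of the problem but does not settle which rule applies to the gaps that remain, and the plan itself expects some.

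**A stronger inference about long stays.** A reader might infer that the rule mainly removes long stays, since more days could mean more entries to complete. The documents do not support this. The clinical variables are listed in a supplementary chart that is not shown. Days on a drug or ventilator could be derived from start and stop dates, and short stays could equally be the incomplete ones. The only stated rule that removes long stays is the separate 90-day exclusion.

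**A stronger inference about the arms.** A reader might also infer unequal completeness from the run-in: control units start official collection after "2 weeks, while the centers participating in the intervention group will have" a further 2 weeks of pilot. Those added weeks bring telerounds into the routine, and nothing shows a lasting difference in blanks. The 0.18–0.24 days above come entirely from the assumed two-fold difference in rates.

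**Conclusion.** The point holds as an inconsistency in the plan. The eligibility exclusion conflicts with the available-data rule and sits badly with the promised intention-to-treat analysis. Read literally, it discards known primary outcomes after randomisation in an open-label trial. This rests on the text alone.

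Selection by stay, severity or arm is a risk of unknown direction and size. Under the mechanisms tried, a true difference of 2.3 days moved to between about 2.14 and 2.45 days. That range shows sensitivity to assumed missingness and assumed control means, and is not an estimate of bias. Loss of power is not the issue: 80.8% to 78.1% if 30% were lost at random without replacement. The article does not say whether excluded children are replaced. If they were, up to 100 per unit, the calculated power would not change, but the analysed children would still be selected. The change should be made, although nothing here shows that the trial's result would be overturned.

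**What to change.** - Delete the incomplete-record and missing-data clause from the exclusion criteria, or limit it to a missing PICU admission or discharge date. State that the discharge date means the date of leaving the unit alive or dead, since the eligibility criteria admit children who die.
- Analyse the primary outcome by intention-to-treat in every otherwise eligible, consenting child with both dates.
- Analyse each secondary outcome in all children with that outcome recorded, as the missing-data section already implies.
- Report missingness and exclusions, with reasons, by arm and by cluster.

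The cost is a wording change and minor extra reporting. Sample size and data collection stay as they are.
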